### 150 **Sample Size Calculation**

151 The frequency of the composite primary outcome in the participating Italian neonatal units is about  
152 47% (severe IVH 8.0%, BPD 24.4%, mortality 14.6%). Meta-analyses showed a reduction of 32%  
153 in in-hospital mortality and of 17% in any IVH in preterm infants assisted at birth with delayed cord

154 clamping instead of immediate cord clamping (6;24). Moreover, no data on the incidence of  
155 outcomes between UCM and delayed cord clamping is available. Thus, we arbitrarily hypothesized  
156 that neonatal assistance with PCI might decrease the frequency of the composite primary outcome  
157 from 47% to 28%. Considering a dropout rate of 5%, we calculated that 106 newborns must be  
158 enrolled in each group to detect this difference as statistically significant with 80% power at a level  
159 of 0.05 using a 2-sided chi-square test.

160

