## 2.3 STUDY OBJECTIVES

### 2.3.1 Primary objective

To compare in the two groups of preterm infants in which assistance with intact placental circulation or assistance after cord milking has been given the proportion of subjects experiencing at least one of the following events at 36 weeks of post-conceptual age: grade 3 or 4 intraventricular haemorrhage (IVH), moderate or severe bronchopulmonary dysplasia (BPD) or death from any cause (composite outcome).

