## 2.7 SAMPLE SIZE

Assuming a proportion of events (grade 3 or 4 IVH, moderate or severe BPD or death from any cause) equal to 47% in the control arm and equal or less than 28% in the experimental arm, corresponding to a relative reduction of the unfavourable events equal to 40%, it was calculated that a sample size of 200 preterm infants (100 per group) would have guaranteed a study power equal to 80%, with a two-sided alpha error equal to 5%, for a standard chi-square test for heterogeneity.

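### The 47% control rate equals the plain sum of three component rates; unless those rates are mutually exclusive it is an upper bound, and the stated 80% power is not supported

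*Combined protocol and SAP*

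**What the plan says.** The protocol's Sample Size Calculation presents the figure as an observed rate for the endpoint itself in the units taking part, and writes it as "47% (severe IVH 8.0%, BPD 24.4%, mortality 14.6"%). It then assumes a fall to 28%, a target it describes as arbitrary. With 5% dropout it arrives at 106 infants per group for 80% power with a two-sided chi-square test at 0.05.

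SAP 2.7 carries the rates forward as "equal to 47% in the control arm and equal or less than 28% in the experimental arm". It also expresses this effect on the relative scale, as a 40% reduction. The number it gives is "a sample size of 200 preterm infants (100 per group"). By its account, that number "would have guaranteed a study power equal to 80"% at a two-sided alpha of 5%. It does not mention dropout.

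SAP 2.3.1 defines the endpoint as the proportion of infants with "at least one of the following events at 36 weeks of post-conceptual age": grade 3 or 4 IVH, moderate or severe BPD, or death. SAP Appendix 1, Table 3.1 has separate rows for IVH with BPD, IVH with death, BPD with death, and all three.

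**The concern.** The rate of at least one event equals the sum of the component rates only when no infant has two of the events. Any overlap makes the composite rate smaller than the sum. Here the quoted composite matches the sum to the decimal, although Table 3.1 provides for infants with more than one event. Neither document gives a joint frequency, says that the components were coded exclusively, or explains how 47% was obtained.

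What is at stake is how the result is read. If the true control rate is lower, the SAP's 40% relative reduction is a smaller absolute difference, and the same number of infants has less power to detect it. A null result would then be reported as coming from a trial with 80% power when the stated inputs do not establish that. The test, the type I error and the estimate are unaffected.

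**Working it through.** **Inputs.** From the protocol's Sample Size Calculation: 8.0%, 24.4%, 14.6%, 47%, 28%, two-sided alpha 0.05, 80% power, 5% dropout, 106 per group. From SAP 2.7: 100 per group and a 40% relative reduction. The overlap between components is not given and has to be assumed.

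**Step 1: reproduce the plan.** Two-proportion chi-square test, pooled variance under the null, no continuity correction:

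n = [1.96·√(2p̄(1−p̄)) + 0.842·√(p₁(1−p₁)+p₂(1−p₂))]² / (p₁−p₂)²

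With p₁ = 0.47, p₂ = 0.28 and p̄ = 0.375, the two roots are 0.6847 and 0.6713. This gives n = 100.7, or 101 per group. Dividing by 0.95 gives 106 from 100.7 (107 from 101). Power at 100 per group is Φ[(0.19·√100 − 1.96·0.6847)/0.6713] = Φ(0.83) = 79.7%. The plan's arithmetic is sound, and the doubt concerns one input.

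**Step 2: the sum.** 8.0 + 24.4 + 14.6 = 47.0.

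**Step 3: the at-least-one rate under assumed overlap.**

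- A. Severe IVH independent of the other two; BPD and death exclusive: 1 − 0.92 × (1 − 0.390) = 43.9%.
- B. All three independent: 1 − 0.92 × 0.756 × 0.854 = 40.6%.
- C. Every severe IVH in an infant who also has BPD or dies; BPD and death exclusive: 24.4 + 14.6 = 39.0%.

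**Step 4: power at 100 analysed per arm, same formula.** The relative reduction is the one implied by 28/47 (1 − 0.596 = 40.4%).

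| Control rate | Same relative reduction | Fixed 28% target | Fixed 19-point difference |
|---|---|---|---|
| 47.0% (no overlap) | 79.7% (to 28.0%) | 79.7% | 79.7% (to 28.0%) |
| 43.9% (A) | 75% (to 26.1%) | 65% | 81% (to 24.9%) |
| 40.6% (B) | 70% (to 24.2%) | 47% | 83% (to 21.6%) |
| 39.0% (C) | 68% (to 23.2%) | 38% | 84% (to 20.0%) |

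Worked example, scenario C with the same relative reduction: the difference is 0.158 and the roots are 0.6547 and 0.6452, so power is Φ[(1.577 − 1.96·0.6547)/0.6452] = Φ(0.455) = 68%.

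If all 106 per arm are analysed, the relative-reduction column becomes 82%, 78%, 73% and 70%.

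**Step 5: are A to C bounds?** No. A and C take BPD and death as exclusive, but Table 3.1 has a row for both. With severe IVH nested and BPD and death independent, the rate is 1 − 0.756 × 0.854 = 35.4% (power 62% at 100 per arm, same relative reduction). The strict minimum is the largest single component, 24.4% (power 42%).

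**Step 6: the two sample sizes.** 106 × 0.95 = 100.7 per arm, and 212 × 0.95 = 201.4 in total. SAP 2.7 quotes the number before dropout, and the protocol quotes the number enrolled.

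**The case against.** The strongest reply is that the documents do not show any overlap in the historical data. The protocol presents 47% as the frequency of the composite, and a breakdown that puts each infant in one category would also add up exactly. Table 3.1 is an empty shell for the trial's results. It shows that combinations are foreseen, not how the units tabulated their past rates. This stands, and it is why the point must be conditional. It does not answer the point, because the exclusive reading is not stated either and the agreement with the sum is exact.

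A second reply is that the shortfall depends on the effect scale. This also stands: with a fixed 19-point difference, power rises slightly. The protocol's 47% to 28% could be read that way, but the SAP states the effect as a 40% relative reduction and as a rate of at most 28%. Power falls on both of those.

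A third reply is that enrolment is complete and the odds ratio with its 95% CI will show the precision achieved. That is true, and it limits the remedy to wording.

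A reader might go further in three ways that the documents do not support. One is to see the 200 and 212 as a conflict; Step 6 reconciles them. Another is to take 5% off the SAP's 100 and compute power at 95 per arm; that applies the dropout to a number that already excludes it. The third is to assume that 24.4% includes mild BPD. The protocol gives no severity and the SAP requires moderate or severe disease, but both cite the same diagnostic definition, so what the figure covers is unknown.

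**Conclusion.** The point holds in conditional form. The 47% is the largest value the at-least-one rate can take given the quoted components, and it is correct only if no infant in the source data had two of the events. Without that statement, the 80% power in both documents is not supported.

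The illustrative size, at 100 analysed per arm, is about 68% to 75% for the SAP's relative reduction and 38% to 65% for a fixed 28% target, with no loss for a fixed 19-point difference. These figures rest on assumed overlap and are scenarios, not limits; 39% in particular is not a floor.

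A reader might infer that the trial has been shown to have less than 80% power. The documents do not support that: the overlap is unknown and the answer depends on the effect scale. The calculation itself reproduces.

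**What to change.** In the protocol's Sample Size Calculation and SAP 2.7:

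1. Keep 47% on record as the planning assumption, and add the observed proportion of infants with at least one event in the same unit data, using the SAP's moderate or severe BPD definition. If that proportion is 47%, one sentence saying so closes the point.
2. If it cannot be tabulated, state that 47% assumes no overlap and is an upper bound.
3. State power conditionally and name the effect scale, for example: about 68% to 80% for a 40% relative reduction at control rates of 39% to 47%, with 100 evaluable per arm. Label the range as illustrative.
4. Add a clause that 212 randomised less 5% dropout leaves about 200 evaluable.

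The cost is wording in two sections and one tabulation from the units' own historical data. The endpoint, the analysis and the enrolment stay as they are. The stated power may look less favourable.

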## 161 **TREATMENT OF SUBJECTS**

### 162 **Randomization**

163 Infants at each unit are randomly assigned in blocks to a treatment group (PCI or UCM) in a 1:1  
164 ratio. The allocation sequences consist of computer generated random numbers. Since the  
165 frequency of the composite primary outcome is inversely related to gestational age, the inclusion  
166 of patients is balanced in each treatment group according to the following gestational ages: 23+0  
167 to 26+6 weeks or 27+0 to 29+6 weeks.

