209 minutes (17) and 85% by 10 minutes of life (18) with a heart rate  $>100$  bpm, despite nasal CPAP  
210 at 5-8  $\text{cmH}_2\text{O}$ .

211 A pulse oximeter (Radical-7, Masimo Corporation, USA) is positioned on Lifestart trolley, and the  
212 trolley, together with all devices placed on it, is covered with a transparent sterile coverage in case  
213 of cesarean section. Thus, the obstetrician hands place the newborn on a completely sterile trolley  
214 and then come back to the mother abdomen, at that moment the neonatologist begin to assist the  
215 baby (with aspiration if necessary, positioning pulse oximeter probe, starting nCPAP/PPV as  
216 necessary). Heart rate will be assessed by auscultation and pulse oximeter. For babies assisted  
217 with an intact cord on Lifestart trolley two person provide bedside neonatal assistance (1 doctor  
218 and 1 nurse). During the 3-minutes period of delayed cord clamping the prevalent procedure will be  
219 to assist respiratory function with nCPAP/PPV till intubation if necessary. If necessary, an early  
220 surfactant administration will be performed in delivery room, but not during the 3-minutes period of  
221 delayed cord clamping.

222 Daily clinical care of the enrolled patients will be performed by the attending physicians in  
223 accordance with the common practice at each center. Daily fluid intake will be started at 80-90  
224 ml/kg and gradually increased by 10–20 ml/kg/day based on changes in body weight, serum  
225 sodium concentrations, and osmolality, with a target intake of 150–160 ml/kg at the end of the  
226 first week of life. In case of hypotension refractory to the fluid-replacement therapy, dopamine

227 and/or dobutamine treatment will be provided. For the treatment of respiratory distress syndrome  
228 (RDS), infants will receive oxygen therapy, respiratory support, and rescue surfactant treatment  
229 to achieve the following therapeutic targets: PaO2 50–60 mmHg, PaCO2 < 65 mmHg, pH > 7.20,  
230 and SpO2 90–95 %. To maintain an adequate SpO2, infants with an FiO2 ≥0.30 will be treated  
231 with surfactant (200 mg/kg Curosurf, Chiesi Pharmaceuticals, Parma, Italy) through the  
232 intubation-surfactant-extubation (INSURE) procedure or less invasive surfactant administration  
233 (LISA) strategy. All infants who will need MV will be treated with surfactant and will then be  

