## 248 **Participant timeline**

249 The patients enrolled in the trial do not receive extra laboratory tests. A heart ultrasound is  
250 performed in the first 24 hours of life and then repeated until PDA closure or as needed. The  
251 direction of ductal shunt, right and left ventricular stroke volume, and superior vena cava flow are  
252 recorded at the first heart ultrasound. All echographic studies are performed in participating centers  
253 by pediatric cardiologists or by neonatologists trained and certified for neonatal echocardiography,  
254 fulfilling the current recommendations for echocardiography training in the NICU (19).  
255 Serial cerebral ultrasounds for evidence of possible IVH and/or PVL are performed in the first 24  
256 hours of life, at 2, 3, 6, 7 (±1), 15 (±2), and 30 (±2) days of life, and at 40 weeks post-conception.  
257 We will collect severe IVH but also Grade 1 and 2 IVH. We will consider only local reads.  
258 Cerebral oxygenation monitoring by near infrared spectroscopy is performed as soon as possible  
259 after the admission of the newborn in NICU and last 24 hours.

260

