### 5.2.2 Primary efficacy analysis

Data regarding the primary efficacy variable will be presented by treatment group and will be reported for the ITT and PP populations. Evaluations on the PP population would be considered as sensitivity analyses.

The distribution of patients by the incidence of composite endpoint will be summarized by frequencies and percentages. Percentages will be calculated according to the total number of patients assigned to each interventional group and to the total number of patients included in the specific analysis population. The 95% CI of the percentage will be calculated according to the exact method.

The proportions of events occurred in the two interventional arms will be compared with the chi-square test for heterogeneity or the Fisher's exact test, if appropriate.

The estimate of the odds ratio and its 95% Wald CI will be obtained with a logistic regression model with the interventional arm as independent covariate. The umbilical

cord milking arm will be treated as reference group. The Wald chi-square test will be used to test the effect of the experimental intervention.

With the intent to verify if a heterogeneity of the experimental treatment effect exists in strata identify by gestational age (23-26 wks. versus 27-29 wks.) and type of delivery (vaginal versus caesarean), two subgroup analyses will be performed with a logistic regression model including the interventional group, the stratification variable, and their interaction term. The odds ratios of event and their 95% Wald CI will be estimated in each stratum and the interaction test will be used to test the heterogeneity of the strata-specific treatment effects.

No adjustment for multiplicity will be adopted.

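### The protocol blocks randomisation by unit, the SAP describes minimisation on gestational age alone, and no planned test uses unit; the analysis should follow whichever scheme was used

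*Combined protocol and SAP*

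**What the plan says.** **Allocation, protocol (Randomization).** "Infants at each unit are randomly assigned in blocks to a treatment group (PCI or UCM) in a 1:1" ratio, with each arm also balanced over two gestational-age bands (23+0 to 26+6 and 27+0 to 29+6 weeks). On this account unit is an allocation factor.

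**Allocation, SAP 2.8.** Written in the past tense: a minimisation algorithm with a random component, run through a central web system, with the same gestational-age bands as the stratification factor. Unit is not listed.

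**Analysis.** For the primary endpoint SAP 5.2.2 says "The proportions of events occurred in the two interventional arms will be compared with the chi-square test for heterogeneity", or Fisher's exact test. The odds ratio comes from a logistic model with arm as the only covariate. The subgroup models add gestational age or type of delivery with an interaction, but not unit. SAP 5.2.3 uses the same tests for the components, and chi-square, Fisher or Wilcoxon tests for the rest. The protocol's Statistical Analysis section is no different. Among the planned displays, centre appears only in descriptive Table 1.4 and in the patient listings.

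**Where units may differ.** Under Study Procedures, daily care is given in "accordance with the common practice at each center". For cerebral ultrasound, the Participant timeline says "We will consider only local reads".

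**The concern.** When allocation is balanced within units, differences in risk between units largely cancel out of the comparison of arms. A test that ignores unit still counts that variation as noise. It then rejects less often than its nominal level and gives up some power. Two parts of the composite could vary by unit: BPD through respiratory practice, and severe IVH through local grading.

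If unit played no part in allocation, the logic changes. Chance imbalance of units between arms is then real noise, and the unstratified standard error already measures it. The test is valid, and stratifying by unit is only a possible gain in efficiency.

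So the disagreement between the two documents decides whether leaving unit out is a mismatch between design and analysis or an acceptable choice. At stake are a few points of power and a primary test that can be defended as following the randomisation. Inflation of false positives is not at stake.

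**Working it through.** **1. The plan's own figure.** SAP 2.7 assumes event rates "equal to 47% in the control arm and equal or less than 28% in the experimental arm", with 80% power and two-sided alpha 0.05. With pooled variance under the null:

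n = [1.96·√(2·0.375·0.625) + 0.842·√(0.47·0.53 + 0.28·0.72)]² / 0.19² = (1.342 + 0.565)² / 0.0361 ≈ 100.7, so 101 per arm.

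The SAP states 100, and power at 100 per arm is 79.7%. With 5% dropout, 100/0.95 = 105.3, giving the protocol's 106. The figures reproduce, and they rest on an unstratified chi-square test.

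**2. Effect of leaving unit out.** From the documents: 200 infants, 8 units, 47% v 28%. Assumed, because the documents do not give them: normal unit effects on the log-odds scale with SD 0 to 1.0, eight equal units of 25, and blocks of 4. Marginal rates are held at 47% and 28%, with 40,000 simulated trials per setting (Monte Carlo error about 0.1 points for error rates and 0.2 for power). The two tests are:

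- chi-square: Z = (p₁ − p₀)/√[p̄(1 − p̄)·2/100]
- Cochran-Mantel-Haenszel (CMH) by unit k: Z = Σ(y₁ₖ − n₁ₖmₖ/tₖ)/√Σ[n₁ₖn₀ₖmₖ(tₖ − mₖ)/(tₖ²(tₖ − 1))]

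Here y₁ₖ is the number of events in one arm of unit k, n₁ₖ and n₀ₖ are the arm sizes, mₖ is all events and tₖ all infants in that unit. Type I error is taken at 47% in both arms. Power changes are computed before rounding.

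| Unit SD | Control rate at ±1 SD | Blocked: chi-square error | Blocked: power, chi-square → CMH | Change | Unit not a factor: chi-square error | Unit not a factor: power, chi-square → CMH | Change |
|---|---|---|---|---|---|---|---|
| 0 | 47% | 5.5% | 80.1 → 79.9 | -0.3 | 5.5% | 79.9 → 78.4 | -1.5 |
| 0.2 | 42–52% | 5.4% | 80.4 → 80.3 | -0.1 | 5.4% | 79.9 → 78.7 | -1.1 |
| 0.4 | 37–57% | 5.3% | 80.8 → 81.2 | +0.4 | 5.4% | 80.3 → 79.8 | -0.5 |
| 0.6 | 33–62% | 4.5% | 81.5 → 82.8 | +1.4 | 5.6% | 80.5 → 81.5 | +1.0 |
| 0.8 | 28–66% | 4.3% | 81.3 → 83.8 | +2.5 | 5.6% | 80.4 → 83.1 | +2.7 |
| 1.0 | 24–70% | 3.6% | 82.2 → 86.0 | +3.9 | 5.3% | 80.4 → 84.7 | +4.3 |

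The CMH error rate stays between 4.8% and 5.2% throughout. Simulations at SD 0.5, 0.7 and 1.0, including one with unequal units of 12 to 40 infants, agree. Under blocking the chi-square error was 4.7–4.8%, 4.3–4.4% and 3.5%, and the CMH gain was about 1, 2 and 3.7 points.

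**3. Intervals.**

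- *Difference in proportions* (Appendix 1, note 2). With blocking and no treatment effect, the ratio of the unstratified standard error to the true SD is 1.01, 1.03, 1.05 and 1.08 at unit SD 0.4, 0.6, 0.8 and 1.0. Under 47% v 28% it is 1.01, 1.02, 1.03 and 1.03. If unit was not a factor, the null ratio is 0.99 to 1.00. The SAP plans an exact interval, so these ratios are only a guide.
- *Odds ratio.* With blocking and SD 0.8 (3,000 runs), adding unit to the logistic model raises the standard error of the log odds ratio from 0.305 to 0.332 (0.332/0.305 = 1.09) and moves the odds ratio from 0.429 to 0.375. The ratio of estimate to standard error goes from 0.846/0.305 = 2.77 to 0.981/0.332 = 2.95, and power from 81.6% to 84.6%. The log-scale interval widens; the gain comes from the larger conditional effect.

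**4. Gestational age.** It is an allocation factor in both documents, and the protocol names it as prognostic, yet the primary test omits it. Assuming 40% of infants in the younger band, control rates of 55% v 42% leave the chi-square with 5.3% error and 79.9% power, against 80.1% when stratified. At 67% v 34% the figures are 4.3% and 81.1% v 84.0%; at 75% v 28%, 3.2% and 82.2% v 87.8%.

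**5. Rare components.** The protocol puts severe IVH at 8.0%, about 16 events in 200. With eight units of 25, the chance that at least one unit has no event is 1 − (1 − 0.92²⁵)⁸ = 1 − (1 − 0.124)⁸ ≈ 65%. That unit's fixed effect cannot then be estimated.

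**The case against.** The case against is substantial. SAP 2.8 describes what was done, in the past tense and in operational detail, and may well be the accurate account. If so, ignoring unit is valid: the error rate stays at about 5.3% to 5.6% for every unit SD tried, against 5.5% with no unit differences. That stands, and it is why the recommendation below is conditional.

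The protocol also standardises much of the care: delivery-room support, blood-gas and saturation targets, surfactant, ventilation and extubation criteria, fluids and antibiotics. IVH and BPD follow published classifications, and cerebral scans are made by clinicians not involved in the infant's care. Large unit differences are therefore possible but not shown, and an SD of 1.0 is the far end of the assumed range. With small differences, stratifying by unit gains nothing or costs a little. Gestational age is the better supported stratification factor.

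A reader might infer from the protocol's wording that the error bars are certainly too wide and that planned power is lost. The documents do not support that. The first part needs blocking by unit and real unit differences, and it is untrue of the planned odds-ratio interval on the log scale. The second fails because the plain chi-square keeps about 80% power in every setting.

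These objections do not remove the contradiction between the documents. Nor do they justify ignoring unit if the protocol's account is the true one.

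**Conclusion.** The documents contradict each other on whether unit was an allocation factor, and no planned test uses it. If allocation was blocked by unit and units differ (assumed SD of unit log-odds 0.5 to 1.0), the plain chi-square is conservative, with a type I error of about 4.8% down to 3.5%. The interval for the difference in proportions is then somewhat too wide, and about 1 to 4 points of power are forgone, with the planned 80% about kept. If unit was not an allocation factor, the unstratified error rate is about right, and stratifying by unit changes power by about -1.5 to +4 points as the SD goes from 0 to 1.0.

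This is lost efficiency and a possible mismatch between design and analysis, not a threat to validity. The sizes rest on assumed unit variation, and all but one simulation on equal unit sizes. Stratifying jointly by unit and gestational-age band (2 × 8 = 16 strata, averaging 200/16 = 12.5 infants) was not simulated.

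**What to change.** State in the SAP which allocation scheme was used, and reconcile it with the protocol's Randomization section. Then, before database lock:

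- **If unit was an allocation factor:** in SAP 5.2.2 make the primary test a CMH test stratified by unit together with gestational-age band, with a matching stratified or conditional logistic odds ratio. In 5.2.3 use van Elteren (stratified Wilcoxon) tests for continuous variables. Keep the unstratified results as supportive.
- **If unit was not an allocation factor:** pre-specify the unit-stratified analysis as a sensitivity analysis.
- **Rare components such as severe IVH:** use CMH or conditional logistic regression, not eight fixed unit effects.

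The cost is SAP wording and a few lines of SAS; centre is already recorded. The downsides should be stated: the odds ratio becomes conditional on the strata, its log-scale interval is wider, and up to about 1.5 points of power are lost if units do not differ.
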